**Fig. 1 Fig1:**
[figure not shown]
Flow of participants

### Quantitative study

Computer-assisted telephone interviewing (CATI) was used on an offline computer to ensure a high level of data protection (offline version of LimeSurvey 2.50+). The participants of the quantitative study were questioned via telephone at four measurement points (at the end of the clinical treatment (t0), after 6 months (t1), 12 months (t2) and 18 months (t3), see Fig. 1). Baseline data collection took place between August 2016 and November 2017. Each telephone survey took 30 min on average. Participants received an immediate expense allowance of 25 Euro after completing each survey.

#### Quantitative measurements

Table 1 presents the selected questionnaire measures, their possible range (if appropriate) and measurement points. Baseline measurement included the following questions about socio-demographic and job characteristics: sex, age, education, partnership, cohabitation, monthly net household income, occupation, weekly working time, working time model, sedentary work, managerial function, tenure, enterprise sector and company size. Two demographic characteristic questions were asked at t1: type of health insurance (statutory or private) and “Are you a civil servant (yes or no)?”. All three follow-up questionnaire measures were modified according the participants´ RTW status (see the footnotes in Table 1 for the selected variables).

RTW-related questions included the RTW expectation: “When do you expect to return to your 1) previous company and 2) previous workplace considering your current state of health - within the next 3, 6, 9 or 12 months?”. To assess work ability, the single-item WAS score was used (“current work ability compared with the lifetime best”), with a possible range of 0 (completely unable to work) to 10 (work ability at its best) [41]. A German version of the RTW self-efficacy scale [42] was used, translated by the study team and verified in terms of accuracy through a third party translator. Job crafting (JC) was measured with a modified and shorter version of a German translation [43] and the JC scale [44]. Questions regarding GRTW and RTW−/BEM processes covered the offer, the concrete procedure and satisfaction with it. Employer to employee contact during SA was measured with two questions concerning 1) who has been contacted through the participant and 2) who contacted the participant and one additional question evaluating the helpfulness of each contact on a four-point Likert scale from (1) not helpful at all to (4) very helpful. Helpful (on the four-point Likert scale from above) and necessary work accommodation needs for RTW were questioned at t0 and necessary work accommodation needs for next 2 years were questioned at t3.

Health-related characteristics included the first and second medical diagnoses (ICD-10 codes) through the clinicians. Recurrence of disorder was defined as “no” if the answer to the question “In which year was the diagnosis of your disorder/illness first made?” was 2016 or later and as “yes” if the answer was before the year 2016. Work-relatedness of disorder was measured on a five-point Likert scale from (1) not at all, (2) slightly, (3) moderately, (4) very to (5) extremely. Sickness absence was measured in weeks, at baseline for the last 12 months and at each follow-up for the last 6 months, respectively. Sickness presenteeism was measured with the question “Has it happened over the previous 6 months that you have gone to work despite feeling that you really should have taken sick leave due to your state of health?” with four answering options (1) never, (2) once, (3) two to five times and (4) more than five times [46]. Self-rated health was measured with the question “How would you describe your current health?” on a five-point Likert scale from (1) very good, (2) good, (3) satisfactory, (4) poor to (5) bad. Functional ability was measured with two sub-scales (managing and cooperation/communication) from the German version of the Norwegian Function Assessment Scale [48, 49]. Participants were asked if they have a degree of disability and – if not – whether they want to apply for recognition as a disabled person. Stigma resistance was measured with two-items of the internalized stigma of mental illness (ISMI) scale [55].

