Whereas acute psychiatric care has its focus on curative treatment, medical rehabilitation facilities provide help `to improve work ability and prevent disability pensions´ (p. 1, Bethge et al. [33]). Hence, medical rehabilitation has its focus on overcoming functional impairments to increase work and everyday life capacity [32]. A stay in a rehabilitation facility can either follow a psychiatric treatment, or, if a psychiatric treatment is not appropriate (e.g. due to less acute or severe symptoms), one can claim benefits for rehabilitation from the German Pension Insurance, where the need for rehabilitation is checked. If rehabilitation treatment is granted, costs are normally taken on by the German Pension Insurance. Psychiatrists and psychotherapists in an ambulant setting or GPs often initiate a rehabilitation treatment when preventive or acute measures were not successful enough. During a stay in a psychosomatic rehabilitation facility, a psychiatrist or medical psychotherapist has the main responsibility for the entire care process [34, 35].

Patients from the cooperating clinics were eligible for the study when they fulfilled the following criteria: (1) aged between 18 and 60 years, (2) sick-listed for less than 6 months during the last 12 months, (3) part-time (at least 15 h per week) or full-time employment, (4) permanent employment or fixed-term employment for at least 18 months, (5) intending to return to work with the former company and (6) treated for a first diagnosis and no more than one further diagnosis of the following list of disorders: a) depressive episode (F32.0, F32.1, F32.2), b) recurrent depressive disorder (F33.0, F33.1, F33.2), c) agoraphobia with panic disorder (F40.01), d) panic disorder (F41.0), e) generalized anxiety disorder (F41.1), f) mixed anxiety and depressive disorder (F41.2), g) adjustment disorders (F43.2). Patients with other disorders not mentioned under ‘Inclusion Criteria’, any current severe somatic comorbidity, minor employment, further qualification, unemployment or early retirement, without any intention to return to work (e.g. to apply for unemployment benefits) or insufficient knowledge of the German language to participate in a telephone interview were excluded.

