Cooperating clinicians were briefed on the inclusion criteria and they subsequently recruited potential participants from August 2016 until November 2017. After obtaining approval and informed consent from the interested participants, a short paper-pencil questionnaire regarding the qualifying inclusion criteria, documents including the medical diagnoses and the participants’ date of discharge were delivered to the project team.

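### The variable called recurrence records whether the first diagnosis was made before 2016: its look-back lengthens over the enrolment period, and it does not measure recurrence

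*Protocol article*

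**What the plan says.** Under 'Quantitative measurements', recurrence rests on one question: "In which year was the diagnosis of your disorder/illness first made". The code is no for 2016 or any later year, and yes "if the answer was before the year 2016". No item on earlier episodes or remission enters the definition.

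Under 'Recruitment and participants', clinicians "recruited potential participants from August 2016 until November 2017". 'Quantitative study' gives the same window for the interviews: "Baseline data collection took place between August 2016 and November 2017".

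Eligibility restricts recent sick leave ("sick-listed for less than 6 months during the last 12 months"), not time since first diagnosis. The eligible diagnoses include single depressive episodes (F32.x) and "recurrent depressive disorder (F33.0, F33.1, F33.2"), and clinicians supplied the ICD-10 codes for the first and second diagnoses.

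Table 2 reports recurrence in 103 of 286 participants (36.0%): 47 of 169 (27.8%) in the psychiatric group and 56 of 117 (47.9%) in the rehabilitation group, with chi-square 11.21, p < .01 and phi .205.

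**The concern.** There are two separate faults in the rule.

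1. **The cut-off is a calendar date, while enrolment covers 16 months.** Two people with the same time since first diagnosis can receive opposite codes only because one was interviewed later.
2. **The label does not match the content.** Year of first diagnosis says how long ago the disorder was first recognised. It cannot tell one long episode from a second one, and it can contradict the clinician's own F33 code in the same dataset.

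The first aim of the quantitative study is to identify personal, disease-related and work-related determinants of time to return to work (RTW) and sustainable RTW. Recurrence is listed among the health-related measures in Table 1, so it is a candidate determinant. Table 2 already presents it as a significant difference between settings. A reader would take that row to mean that more rehabilitation patients had relapsed, which the question did not establish.

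**Working it through.** **Inputs.** Cut-off of 1 January 2016 ('Quantitative measurements'); interviews from August 2016 to November 2017 ('Quantitative study'); counts not recurrent/recurrent of 122/47 (psychiatric) and 61/56 (rehabilitation) (Table 2).

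**Step 1: reproduce the stated figure.** The percentages reproduce: 103/286 = 36.0%, 47/169 = 27.8%, 56/117 = 47.9%. The 2×2 chi-square with Yates correction is 11.21 (p = 0.0008), as stated. The stated phi is the uncorrected version: √(12.06/286) = .205. The arithmetic of the row is sound; the question is what it counts.

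**Step 2: look-back that still counts as no.** Look-back = interview date − 1 January 2016, with 30.44 days per month.

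- August 2016: 213 to 243 days, or 7.0 to 8.0 months.
- November 2017: 670 to 699 days, or 22.0 to 23.0 months.

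The window lengthens by about 15 months between the same points of the first and last month (670 − 213 = 457 days; 457/30.44 = 15.0).

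**Step 3: code given to the same history at different interview months** (whole months since first diagnosis).

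| Months since first diagnosis | Aug 2016 | Nov 2016 | Jan 2017 | Jun 2017 | Nov 2017 |
|---|---|---|---|---|---|
| 7 | no | no | no | no | no |
| 8 | yes | no | no | no | no |
| 12 | yes | yes | no | no | no |
| 15 | yes | yes | yes | no | no |
| 18 | yes | yes | yes | yes | no |
| 22 | yes | yes | yes | yes | no |
| 23 | yes | yes | yes | yes | yes |

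The inconsistency is confined to first diagnoses about 7 to 23 months before interview. Shorter histories are always no and longer ones always yes.

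**Step 4: what the rule can get wrong about recurrence itself.** Two cases permitted by the eligibility criteria:

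- A single continuous episode first diagnosed in December 2015 and treated in August 2016 is coded yes.
- A disorder coded F33 by the clinician, with the participant giving 2016 or 2017 as the year of first diagnosis, is coded no.

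**Step 5: how much recoding would matter (illustration; the counts are assumptions).** If 10 of the 56 rehabilitation yes codes became no and nothing else changed, the Yates chi-square would be 3.66 (p = 0.056). If instead 14 psychiatric no codes became yes and nothing else changed, it would be 3.49 (p = 0.062); with 13 it would be 3.88 (p = 0.049). Equalising the percentages by psychiatric recodes alone would take 34: (47 + 34)/169 = 47.9%. The article does not show whether one-sided recodes of this size are plausible.

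**The case against.** The strongest reply is that this is one disclosed descriptor with no demonstrated consequence. The question and the rule are both printed, so a reader can see what was coded. The article does not name recurrence as a Cox covariate. Its only documented use is one row of Table 2, which the accompanying results text does not discuss. The ICD-10 codes are held separately, and covariate coding can be settled later. All of this stands, and it keeps the point minor. It does not rescue the label, because the article itself fixes the definition and reports a result under that name.

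A reader might infer that the 27.8% versus 47.9% contrast is biased by enrolment date. That would need the two settings to have recruited at different times, and the article gives no enrolment dates by setting. A reader might also suspect a care-pathway effect, since the article says a rehabilitation stay can follow psychiatric treatment, so that some rehabilitation patients may be further from first diagnosis within the same episode. That is plausible but untested. Nor can it be said that the hazard ratio for recurrence will be attenuated or distorted, because the document does not state that such a model will use this variable.

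A further objection concerns the remedy. Interview year minus diagnosis year looks like the obvious repair, but it keeps most of the fault. The history scored 0 would be about 7 to 8 months in August 2016, 11 to 12 in December 2016, 0 to 1 in January 2017 and 10 to 11 in November 2017. That is a drift of about 12 months with a break at New Year: a first diagnosis in December 2016 with interview in January 2017 would score 1, and an October diagnosis with a November interview would score 0. This objection is right, and that repair is not proposed here.

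**Conclusion.** The point holds in a limited form. The stated rule codes participants first diagnosed about 7 to 23 months before interview differently by enrolment date, and what it codes is time since first diagnosis. The look-back figures follow from the stated dates alone and need no assumption. The two misclassified cases in the fourth step follow from the rule and the eligible diagnoses.

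The number of participants affected cannot be derived, because neither the distribution of diagnosis years nor the enrolment dates are given. The size and direction of any effect on the setting contrast, or on later models, are therefore unknown. The variable is a secondary baseline descriptor and a candidate determinant, and the primary outcome is untouched. Severity: minor.

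**What to change.** Use data already held.

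1. Rename the present variable 'first diagnosed before 2016' wherever it is kept.
2. For depressive disorders, report and use the clinician codes F33.x versus F32.x as the recurrence indicator.
3. For all disorders, if chronicity is to be modelled, use continuous time since first diagnosis (interview date minus the mid-point of the diagnosis year) in place of a calendar-year cut-off. When diagnosis and interview fall in the same year, take the mid-point between 1 January and the interview date, since otherwise an interview before July would give a negative value.
4. Recompute the Table 2 row.

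The cost is a recode of existing fields and one table row; no new data collection is needed. There are two drawbacks. Only the year of diagnosis was asked, so time since diagnosis is accurate to about half a year either way. F33 also carries no recurrence information for anxiety or adjustment disorders, the latter being the first diagnosis of 42 of the 286 participants.

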#### Primary and secondary outcomes

The primary outcome of the quantitative study is the time until RTW and full RTW (after finishing all GRTW measures) measured in days. The secondary outcome is the sustainability of RTW (SRTW), which often has been defined as ‘28 days of full RTW’ or within longer timeframes of 6 months or 2 years of full RTW [56]. Beyond these definitions solely based on administrative timeframes [cf. 18], in the present study a more comprehensive definition of SRTW will be developed and tested with quantitative and qualitative follow-up data.

#### Data management and statistical analyses

Statistical analyses will be performed with SPSS 24 and Stata 15 (or subsequent versions). Descriptive analysis and interrelationships will be examined. Two types of survival analyses will be conducted. A continuous Kaplan-Meier procedure will be used to analyse the period between the date of discharge of the participant from the clinic or the rehabilitation facility and the first day on the job. In the second survival analysis, cox regression survival models will be conducted to investigate the factors that influence the time to RTW and SRTW. To adjust for clinic and clustering, analyses will be performed using multilevel modelling, where the clinic could be included either as a fixed or random effect. SRTW trajectories will be identified using sequence analysis and subsequently analysed in regression models. In all publications, results will be reported following the STROBE statement (Strengthening the Reporting of Observational Studies in Epidemiology) [57]. In the present paper, we describe quantitative and qualitative baseline findings with a non-response analysis and characteristics of the participants stratified by the two examined mental health services, group differences were analysed with chi-square tests and t-tests (see Table 2).

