## Background

Mental disorders are widespread in Germany. Twenty-eight percent of the general population between 18 and 79 years experience one mental disorder within a 12 month time period. The highest prevalence rates are observed among younger age groups, mainly affecting the working age (18–34 years: 36%, 35–49 years: 28%, 50–64 years: 26%, 65–79 years: 20%) [1, 2]. The burden, costs and challenges of mental disorders are high for the affected individuals, their employers, companies and society [3–6]. The processes of successfully returning to work (RTW) and achieving a sustainable RTW (SRTW), therefore, play an essential role in recovery and the prevention of further negative consequences like job loss or disability retirement [7–10].

Germany has a mainly community-based comprehensive mental healthcare system without great financial barriers for its use by the patients. Although the prevalence rates of mental disorders are high, utilisation rates of mental health services in Germany are relatively low, e.g. 33% with any 12-month diagnosis of a mood disorder report a mental health service use within the last 12 months, throughout all diagnoses the number is even lower (19%) [11]. Along with it, the German mental healthcare system is fragmented between various service providers (e.g. general practitioners vs. mental health specialists like psychiatrists or medical / psychological psychotherapists), settings (e.g. in- vs. outpatient care) and funding (e.g. statutory health insurances vs. German Pension Insurance scheme) [12, 13]; for a short overview of sectors and service providers see [11]. Despite the huge burden and costs, RTW and SRTW research at the intersection of the mental healthcare system and workplace has received little attention in Germany so far.

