#### Characteristics of the participants

Table 2 shows the baseline characteristics for the total cohort as well as stratified by psychiatric and rehabilitation group (due to the afore mentioned differences in the care and funding system). At baseline, participants of the rehabilitation group were on average 3 years older, had more fixed working hours or shift work, less sedentary work, a faster RTW expectation, and reported higher RTW self-efficacy, higher work ability, better self-rated health, greater functional ability and less depressive symptoms than the psychiatric participants. Whereas nearly 36% of the rehabilitation participants were diagnosed with an adjustment disorder as their first diagnosis, all participants of the psychiatric group were diagnosed with a depression or anxiety disorder. The average length of a stay in a psychiatric clinic was more than 2 weeks longer (mean = 7.6 weeks, SD = 1.60) than in a rehabilitation facility (mean = 5.2 weeks, SD = .76; *t* (257) = 16.618, *p* < .001, mean diff. = 2.36, 95% CI [2.08–2.64] η^2^ = .493). Most psychiatric participants received day hospital treatment (76%), whereas almost all rehabilitation participants received inpatient treatment (98%). The median monthly net household income was lower in the rehabilitation group: 2000–3000 Euros vs. 3000–4000 Euros in the psychiatric group (Median Test*, p* < .05). Nearly all participants (97%) had a permanent employment contract.

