Recurrence of disorder	Own development		x			
Work-relatedness of disorder	Adapted from Würzburger Screening [45]	1 to 5	x			
Weeks of sickness absence for the last twelve/six months	Own development		x	x	x	x
Sickness presenteeism	[46]		x	x^a^	x^a^	x^a^
Self-rated health	[47]	1 to 5	x	x	x	x
Functional ability	NFAS [48, 49]	1 to 5	x	x	x	x
Depressive symptoms	PHQ-8 [50]	0 to 24	x	x	x	x
Generalized anxiety	GAD-2 [51]	0 to 6	x	x	x	x
Regular physical activity	DEGS [52]		x			
Smoking behaviour	DEGS [52]		x			
Alcohol consumption	Adapted from DEGS [52]		x			
Clinical stay	Adapted from [53]		x			
Comorbidity	Own development		x			
Further treatment	Own development		x	x	x	x
Application for early retirement	Adapted from SPE-Scale [54]			x^c^	x^c^	x^c^
Application for recognition as a disabled person	SIBAR [40]		x			x
Degree of disability	SIBAR [40]		x			x
Stigma resistance	Adapted from ISMI-10 [55]	1 to 4	x	x	x	x

*COPSOQ* Copenhagen Psychosocial Questionnaire, *SIBAR* Screening instrument work and occupation, *WAS* Work ability score, *Würzburger Screening* for Sociomedical Documentation, *PHQ-8* Patient Health Questionnaire Depression Scale-8, *GAD-2* Generalized Anxiety Disorder Scale-2, *DEGS* German Health Interview and Examination Survey for Adults, *ISMI-10* Internalized Stigma of Mental Illness Scale-10. *SPE-Scale* subjective prognosis of gainful employment

^*a*^ only applied if participant did return to work, ^b^ only applied if supervisor changed, ^c^ only applied if participant did not return to work yet

**Table 2 Tab2:** Baseline characteristics of the total study population and stratified by psychiatric and rehabilitation group

Variables	Total sample (*n* = 286)	Psychiatric group (*n* = 169)	Rehabilitation group (*n* = 117)	Statistics^a^
Sociodemographic				
Sex, % (n)				
Female	46.5 (133)	45.6 (77)	47.9 (56)	*n. s.*
Male	53.5 (153)	54.4 (92)	52.1 (61)	
Age^b^ (years), mean ± SD (n)	47.7 ± 8.6 (286)	46.4 ± 8.7 (169)	49.7 ± 8.2 (117)	*t* (284) = −3.25, *p* < .01
≤ 39 years, % (n)	18.5 (53)	22.5 (38)	12.8 (15)	*Χ*^*2*^ (2, *n* = 286) = 14.95, *p* < .01, *V* = .229
40–49 years, % (n)	29.4 (84)	34.9 (59)	21.4 (25)	
≥ 50 years, % (n)	52.1 (149)	42.6 (72)	65.8 (77)	
Highest educational/ vocational qualification^b^, % (n)				
Qualification from a company/ school-based vocational training	48.3 (138)	45.0 (76)	53.0 (62)	*n. s.*
Qualification from a technical college/ vocational academy	18.5 (53)	16.6 (28)	21.4 (25)	

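### Kaplan-Meier is named for time to RTW with no method for participants who can no longer return; if they are censored, the curve overstates the proportion returned

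*Protocol article*

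**What the plan says.** Under Primary and secondary outcomes, the primary outcome is "time until RTW and full RTW (after finishing all GRTW measures) measured in days". Under Data management and statistical analyses, two survival analyses are planned. The first is descriptive: "A continuous Kaplan-Meier procedure will be used to analyse the period between the date of discharge of the participant from the clinic". Discharge from a rehabilitation facility starts the interval in the same way, and the first working day ends it. The second concerns determinants: "cox regression survival models will be conducted to investigate the factors that influence the time to RTW and SRTW". The section names no competing-risks method and no cumulative incidence function, and it gives no rule for participants who become unable to return.

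The article itself makes such exits foreseeable. The Background links RTW to the "prevention of further negative consequences like job loss or disability retirement", and Recruitment and participants justifies the rehabilitation group partly by the rise in disability pensions for mental disorders. Table 1 lists current working status and RTW/SRTW trajectories at all three follow-ups. It also lists "Application for early retirement", asked only of those who have not yet returned.

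**The concern.** A participant who takes a permanent disability pension, or who dies, before returning to work can no longer have the event. Censoring that person at the exit assumes the same later chance of return as for those who are still employed and absent. After a permanent exit that chance is zero. One minus Kaplan-Meier then no longer estimates the proportion of the cohort that returned; it is at or above it.

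What is at stake is the absolute level of the descriptive curve for the primary outcome, overall and by treatment setting. If exits differ between the psychiatric and rehabilitation groups, their curves would be shifted by different amounts. The article says that the two settings should be considered in further analyses, so curves by setting are a likely use.

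**Working it through.** **The plan's own figures.** None bears on this point. The stated 247 events reproduce with the Schoenfeld formula at equal allocation: 4 × (1.960 + 0.842)² / (ln 0.7)² = 31.40 / 0.1272 = 246.8, rounded up to 247. This neither supports nor weakens the concern.

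**Inputs.**
- Estimator and interval: Data management and statistical analyses.
- R, the true proportion returned by 18 months, and C, the proportion leaving by a competing route: neither is in the documents. I assume R = 85% (range 75% to 93%) and C = 1% to 5%, with 10% as a stress case.
- Exits are censored when they occur, the ratio of exit hazard to return hazard is constant, and there is no other loss to follow-up.

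**Formula.** The total cumulative hazard is H = −ln(1 − R − C). The part due to return is H × R/(R + C). Hence 1 − KM = 1 − exp(−H × R/(R + C)) = 1 − (1 − R − C)^(R/(R + C)).

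**Worked case, R = 0.85 and C = 0.05.** H = −ln(0.10) = 2.303. Return part: 2.303 × 0.85/0.90 = 2.175. 1 − KM = 1 − exp(−2.175) = 0.886, which is 3.6 points above 0.85.

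| Assumed exits C (R = 0.85) | 1 − KM | Overstatement, points |
|---|---|---|
| 1% | 0.857 | 0.7 |
| 3% | 0.871 | 2.1 |
| 5% | 0.886 | 3.6 |
| 10% | 0.931 | 8.1 |

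**Sensitivity to R.** For R from 0.75 to 0.93, the overstatement is about 0.5 to 0.8 points at C = 1% and 2.9 to 4.6 points at C = 5%.

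**Sensitivity to timing.** Most participants expect to return early, so I also let the return hazard be high in months 0 to 3, with a constant exit hazard of 0.01 per month.
- Return hazard 0.4 then 0.05 per month: 83.5% return and 4.6% exit. 1 − KM = 1 − exp(−(0.4 × 3 + 0.05 × 15)) = 0.858, an overstatement of 2.3 points.
- Return hazard 0.6 then 0.05 per month: 90.5% return and 3.0% exit. 1 − KM = 1 − exp(−(0.6 × 3 + 0.05 × 15)) = 0.922, an overstatement of 1.7 points.

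Early return therefore makes the error somewhat smaller than the constant-ratio formula gives (3.2 and 2.4 points at the same R and C).

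**The alternative handling.** Take 100 participants: 85 return, 5 exit and 10 do neither. If the 5 stay in the risk set as not returned until 18 months, the curve ends at 15/100 and 1 − KM = 85%. The bias from this source is zero. The choice of rule therefore decides whether the error occurs.

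**The case against.** The strongest reply is that the article never says that exits are censored. Kaplan-Meier does not impose that rule, and a journal article may leave censoring rules to an analysis plan that is not shown. This stands as far as it goes: a reader might infer that the plan itself censors job loss and disability retirement, and the text does not say so. It does not remove the point. The estimator that is named gives the proportion returned only under a special handling that the article does not state, while a better estimator for foreseeable exits is readily available.

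Second, job loss need not compete. The analysis interval ends at the first working day, with no restriction to the former employer. Eligibility required "intending to return to work with the former company", but that describes intention at entry and does not define the endpoint. This stands, so job loss belongs among the competing events only if a new job does not count as RTW. Permanent disability retirement is the clearer case.

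Third, the first quantitative aim is determinants, analysed by Cox regression. This also stands. A Cox model that censors competing exits still estimates a valid cause-specific hazard ratio, so only absolute proportions read from the curve are affected.

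Fourth, the cohort was selected against exits. "Nearly all participants (97%) had a permanent employment contract", and Table 2 shows 83.9% expecting to return within 3 months. This does not settle the rate, but it points to the low end of the range.

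**Conclusion.** The concern holds in a conditional form. The article plans Kaplan-Meier for time to RTW and names no method for participants who lose the possibility of return. If they are censored at exit, the curve overstates the proportion returned. With 85% true return and 1% to 5% exits, both assumed, the overstatement is about 1 to 4 percentage points. It is less if returns are concentrated early, and zero if exits are kept at risk as not returned. It should be corrected, but it does not threaten the analysis of determinants.

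Three stronger readings are not supported:
- **A bias of around 12 points.** This needs 15% exits alongside 80% return (1 − 0.05^(0.80/0.95) = 0.920), which leaves only 5% neither returned nor exited. Nothing in the documents suggests such a rate.
- **Distortion mainly in the sicker setting.** The psychiatric group reports worse health, but the rehabilitation group is older (65.8% against 42.6% aged 50 or over). The direction of any difference is unknown.
- **The same bias in full RTW.** Full RTW is part of the primary outcome, but Kaplan-Meier is described only up to the first working day. The point extends to full RTW only if that is plotted in the same way.

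**What to change.** - Report the Aalen-Johansen cumulative incidence of RTW in place of one minus Kaplan-Meier, with permanent labour-market exit and death as competing events, overall and by treatment setting. Do the same for full RTW if it is plotted.
- Show the cumulative incidence of the competing exits beside it. If exits are rare, the two estimators will nearly coincide and that can be said.
- State whether starting work with a new employer counts as RTW. If it does not, add job loss to the competing events.
- Keep the Cox models and describe their hazard ratios as cause-specific.

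The cost is a little more analysis in Stata, which is already the named software. The practical limit is dates. An application for early retirement is not itself an exit, so the exit date has to come from the working-status and trajectory items, and the article does not show that these always supply one. Where a date is lacking, keep the participant at risk as not returned to the end of follow-up and report how many were handled in this way.
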